#### Randomization and allocation concealment

For part I of the study, two concealed randomizations will be needed; once for the order of the assessors for the inter-tester reliability and once to decide the order of the tested leg for each patient. The concealed block randomization will be performed, in a block size of four with a validated electronic randomization system, and will be performed by a secretary, completely independent of the study and does not have access to raters nor patients. The allocation concealment will be granted by sequentially numbered, opaque, sealed envelopes one pile with white envelopes for the order of the assessors and one with grey envelopes for the order of the tested leg, which the secretary will assign just before the beginning of the testing procedure.

#### Data collection

 The data collection will be performed as soon as the participant officially gave their permission and signed the informed consent. Participants’ information and test results will be entered in the electronic case report form (e-CRF, see “Data handling and storage for part I and part II of the study” section).

##### Sociodemographic data and population characteristics

The socio-demographic data (age, sex, height, and weight) will be extracted from the electronic participant record of the AFFIRM-CT cohort study.

Participants’ fall history in the last 6 months [6] will be obtained by personal questioning with a beforehand explanation of the definition of a fall. A fall is defined as an event resulting in a person inadvertently coming to rest on the ground, floor, or other lower level [2].

Cognitive impairment is known as an influencing factor of the fall risk in older adults [27]. Consequently, the study nurse will assess cognitive impairments with the Mini Mental State Examination (MMSE), a validated assessment tool for older persons [27, 28].

##### Functional fall risk assessments

To complete the data of the participants’ characteristics the study nurse will further assess the SPPB [24] and participants’ usual gait speed on 4m [25, 26]. The SPPB is a functional physical measure of performance for older persons [29] with possible scores ranging from zero (worst) to 12 points (best). For the assessment of the walking speed, participants will be asked to twice walk a 4m distance at their usual speed with a static start [26]. The faster of the two trials will be retained for the analyses [26].

##### Index test; hip abductors strength test

The data collection for the HAS tests is described earlier in the method section. The strength values will be entered in the e-CRF.

#### Sample size calculation for the reliability of the index measure

According to previous study results assessing HAS [30] we are expecting ICC_agreement_ values of 0.8 and above, corresponding to good to excellent reliability for the intra- and inter-tester reliability [20]. For the 95 % confidence intervals, we are expecting values of ± 0.2 which lead us to a sample size of 23, calculated with the statistical environment R [31] (package: ICC sample size), for part I. Considering a 10 % drop out rate, we will include 26 participants. All 26 participants will be assessed for inter-, and intra-tester reliability.

#### Data analysis

Data analyses will be performed with SPSS version 25 (IBM Corp. Released 2017. Armonk, NY: IBM Corp.). Descriptive statistics for the sample characteristics, time to complete the tests, and number of participants able to perform the test will be performed. For continuous variables, we will present the mean and standard deviation (mean ± SD). Intra-tester and inter-tester reliability will be assessed using the ICC_agreement_ (A, 1) model, which assesses the degree of agreement among measurements assuming a two-way random-effects model [15, 32]. In addition, we will compute 95 % confidence intervals (CI) through bootstrapping (5000 resamples, bias-corrected, and accelerated percentile method) [15]. The standard error of measurement (SEM) will be computed as follows: SEM= $$ \surd \left({\sigma}_{observer}^2+{\sigma}_{residual}^2\right) $$ where *σ*_*observer*_ is the variance between the two testers and the residual variance, which is partly due to the unique combination of participants and observers [33, 34]. The minimal detectable change (MDC) will be calculated as follows: MDC = 1.96 ∗ SEM∗ √2. The MDC will be normalized by the mean and expressed in percentage. We will further use Bland Altman analyses to investigate absolute reliability and determine between session agreements of the strength measurements [35, 36]. We will also present the 95 % limits of agreement (LoA 95 %) representing two SD above and below the mean differences between the sessions [30].

### Part II: construct and Criterion Validity

The validation will be performed according to the principles of COSMIN [34] and following the checklist of « Standards for Reporting Diagnostic accuracy studies » (STARD) [37]. The construct we are interested in, in part II of this study, is measuring the “fall risk” of persons aged ≥ 65 years. As indicated in the introduction, falls and fall risk are influenced by a vast number of influencing factors with a very multifactorial etiology (a multidimensional construct). Therefore, “fall risk” is a rather abstract construct, which researchers and clinicians try to assess indirectly by a variety of different tests. Interesting factors for prevention or rehabilitation interventions for “fall risk” are performance variables like balance and strength, which are modifiable by non-pharmacological interventions of health care professionals (e.g. physiotherapists, ergotherapists, etc.) and open to improvement. Therefore, in our field “fall risk” is currently assessed by performance tests like the SPPB [24], the timed up and go (TUG) [38], gait speed (GS) [26], as well as hand-grip strength (HGS) as a parameter, assumed to be related to whole-body strength and fall risk [39, 40]. These tests will be used to assess the construct validity as they are all assumed be measuring one or more aspects of the not directly to measure construct “fall risk”.

For the evaluation of the criterion validity, the fall history will be used as the predefined external criterion also called the reference standard or gold standard in this part of the study. It is assumed to correctly classify the participants into fallers or non-fallers. Participants not reporting a fall in the follow-up phase of the study and/or within the last 6 months will be classified as non-fallers [41]. Participants that report one or more falls will be classified as fallers [41]. Participants were informed that a fall was defined as an event resulting in a person inadvertently coming to rest on the ground, floor, or other lower level [2]. Ideally, fall history is assed in a prospective follow up period where participants can closely be followed and their number of falls regularly assessed.

#### Study aims and hypotheses

For the evaluation of construct validity of the hip abductors’ strength measurement, we will compare the hip abductors strength to other currently used functional fall risk assessments like the SPPB [24], TUG [38], GS [25], and HGS [40]. We aim to assess the strength and direction of the correlation between currently used fall risk assessments SPPB, TUG, GS, and HGS with the hip abductors strength, each separately. We hypothesize to find moderate [42] positive correlations (0.40–0.69) between hip abductors strength, SPPB, GS, and HGS and moderate negative correlations between the TUG and hip abductors strength. We are expecting moderate correlations as HAS assesses the same construct but not completely the same parameters as the other fall risk assessments. SPPB and TUG, and in some ways GS, include the assessment of functional parameters like gait and balance, whereas HGS and HAS assessment include only strength. We expect the correlations between hip abductors, SPPB, GS, and HGS to be positive and hypothesize to find the highest –correlation (close to the upper boundary of a moderate correlation ≤ 0.69) between SPPB and HAS as both include a specific strength assessment of the lower limb. The correlation between HGS and HAS is expected to be rather close to the lower boundary of a moderate correlation (≥ 0.4) as they don’t assess the strength of the same body parts. The correlation between the TUG and HAS is hypothesized to be almost as strong as between the SPPB and HAS but due to the scoring of the TUG in a negative direction.

The criterion validity will be evaluated considering HAS as the index test and fall history of the last 6 months as well as falls during the follow-up time of 12 months as the predefined reference standard. We intend to evaluate if hip abductors’ strength assessed with the new procedure is a good diagnostic tool to classify older persons into fallers and non-fallers and/or can improve fall risk detection by combining it with other functional fall risk assessments. Therefore, for the criterion validity we aim to investigate the diagnostic accuracy of HAS (MVIS and RFG), by evaluating its area under the curve [AUC], sensitivity [sens], specificity [spec], positive predictive value [PPV], negative predictive value [NPV], and positive and negative likelihood ratio [LR+, LR-] and the respective, clinically relevant cut-off values. We will compare these values, in the same population, with the indicators of diagnostic accuracy for TUG, SPPB, GS and HGS. We will further calculate net sensitivity and specificity of HAS to get insight in its possible combination with our chosen fall risk assessments (TUG, SPPB, GS and HGS). We hypothesize to find a good diagnostic accuracy of HAS assessed with the new procedure and AUC values of ≥ 0.85 [16, 43] with a 95 % confidence interval not going below a moderately accurate level of 0.7 [16, 44]. The diagnostic accuracy will be comparable to that of the fall risk assessments TUG, SPPB and GS and has a better accuracy than HGS. Additionally we expect a high accuracy of HAS in recognizing fallers in parallel testing with TUG, SPPB, GS, and HGS [17].

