#### Sample size calculation

According to our previous findings of the AUC of hip abductors strength in a standing position, good AUC values (0.85) are expected [16, 43] with a 95 % confidence interval not going below 0.7 [16]. Using the statistical environment R [31] with a significance level of 5 % and a power of 80 % we need 31 positive and 104 negative cases for the evaluation of the diagnostic accuracy (criterion validity). Compensating for an expected drop-out rate of 20 % over the 12 months follow up period, we will have to include 169 participants. As the sample size calculation for the construct validity is smaller than for the criterion validity we base our study on the sample size for the criterion validity.

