#### Data analysis

Data analyses will be performed with SPSS version 25 (IBM Corp. Released 2017. Armonk, NY: IBM Corp.). Descriptive statistics for the sample characteristics and the functional and non-functional fall related variables will be performed. For continuous variables, the mean and standard deviation (mean ± SD) will be presented.

The definition of the evaluation of the MVIS and RFG of the HAS is described in our previous article [15]. MVIS and RFG will be normalized to body weight [16].

For the construct validity, the correlations of the HAS (MVIS and RFG) with the functional fall risk assessments SPPB, TUG, GS, and HGS will be presented.

For the criterion validity, the AUC and the diagnostic values of HAS, TUG, SPPB, GS, and HGS, compared to the chosen external criterion, history of falls, and 12 months fall prediction (sensitivity, specificity, PPV, NPV, LR+, and LR-) as well as cut-off values will be presented. We will further calculate the net sensitivity and net specificity to present the additional use of HAS in a test battery with other fall risk assessments (SPPB, TUG, gait speed). Additionally we will calculate indices for calibration and discrimination.

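### Comparable accuracy of HAS with TUG, SPPB and GS is hypothesised, but the plan presents AUCs test by test, sets no margin, and sizes the study only for the single HAS AUC

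*Protocol article*

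**What the plan says.** Three places in Part II of the protocol article bear on this.

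- **Study aims and hypotheses.** HAS is to be set against the other tests: "We will compare these values, in the same population, with the indicators of diagnostic accuracy for TUG, SPPB, GS and HGS". The expected result follows: "The diagnostic accuracy will be comparable to that of the fall risk assessments TUG, SPPB and GS". The same sentence expects HAS to do better than HGS. No margin or other definition of comparable is given.
- **Data analysis.** The output for criterion validity is "the AUC and the diagnostic values of HAS, TUG, SPPB, GS, and HGS, compared to the chosen external criterion", followed by sensitivity, specificity, predictive values and likelihood ratios; these "as well as cut-off values will be presented". No difference between AUCs, and no interval for one, is mentioned.
- **Sample size calculation.** The basis is the HAS test alone: "good AUC values (0.85) are expected". A condition on precision is attached to that expectation, namely "with a 95 % confidence interval not going below 0.7". The case numbers, derived for 80% power at the 5% level, are 31 fallers and 104 non-fallers. With 20% drop-out this becomes 169 participants. The only other remark is that construct validity needs fewer participants. The comparison between tests is not sized.

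**The concern.** The hypothesis is one of similarity. Two AUCs that look alike, or a difference that is not significant, are weak evidence of similarity when the difference is imprecise. The less precise the study, the more easily the tests look alike, so imprecision favours the result the investigators expect. All tests are performed on the same participants. The paired difference and its interval can therefore be computed without further data, and they are the quantities that answer the question. At stake is whether the report can say that HAS is as accurate as tests already in use, a statement clinicians would rely on when choosing a fall-risk test.

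**Working it through.** **Inputs.** From the sample size section: 31 fallers, 104 non-fallers, HAS AUC 0.85, reference value 0.70, 5% significance, 80% power, 20% drop-out. From the Part II hypotheses: correlations of HAS with the other tests of 0.40-0.69 in absolute value, highest (near 0.69) for SPPB, almost as strong for TUG, near 0.40 for HGS; GS has no value of its own within the range. Assumed: a comparator AUC of 0.75. The Discussion calls the accuracy of SPPB and TUG moderate but gives no figure.

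**Step 1: reproduce the plan's figure.** The Hanley-McNeil variance of an AUC *A* is

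V(A) = [A(1−A) + 30(P₁−A²) + 103(P₂−A²)] / (31×104), with P₁ = A/(2−A) and P₂ = 2A²/(1+A).

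- A = 0.85: (0.1275 + 0.4989 + 6.0339)/3224 = 0.002066, SE 0.0455
- A = 0.75: (0.1875 + 1.1250 + 8.2768)/3224 = 0.002974, SE 0.0545
- A = 0.70: (0.2100 + 1.4538 + 8.9065)/3224 = 0.003279, SE 0.0573

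Power for 0.85 against 0.70, two-sided 5%: Φ[(0.15 − 1.96×0.0573)/0.0455] = Φ(0.83) = 79.7%. The drop-out step is 135/0.80 = 168.75, so 169. Both stated figures reproduce for the single-AUC question.

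**Step 2: paired difference at the same size, by formula.** With *r* the correlation between the two AUC estimates, SE(d) = √(V₁ + V₂ − 2r√(V₁V₂)). For 0.85 and 0.75 at r = 0.5:

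SE(d) = √(0.002066 + 0.002974 − 0.002479) = 0.0506; half-width 1.96×0.0506 = 0.099; power ≈ Φ(0.10/0.0506 − 1.96) ≈ 51%.

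The same formula gives 44% at r = 0.4 and 60% at r = 0.6. A binormal variance gives 41%, 48% and 57% at r = 0.4, 0.5 and 0.6. The formula is symmetric, so it makes no difference which test has the higher AUC of the pair.

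**Step 3: simulation.** Binormal scores, 31/104, true AUCs 0.85 and 0.75, DeLong variance, two-sided 5%. The correlation here is between test scores within fallers and within non-fallers.

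| Within-group correlation | Gap of 0.10 missed |
|---|---|
| 0.3 | 55% |
| 0.4 | 50% |
| 0.5 | 43-44% |
| 0.6 | 35% |
| 0.7 | 24-25% |

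An overall correlation of 0.69 corresponds to about 0.63 within groups, where the gap is missed in 32-33% of studies. An overall correlation of 0.40 corresponds to about 0.26 within groups, with a miss rate of 55%. Across true AUCs of 0.75-0.85 and correlations of 0.3-0.7, the 95% half-width of the paired difference is about 0.06-0.12.

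**Step 4: reading separate intervals side by side.** If each AUC were shown with its own 95% interval and overlap were taken as comparability, a true gap of 0.10 would still show overlap in about 89-98% of studies (0.85 vs 0.75 and 0.80 vs 0.70, overall correlations 0.40-0.69).

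**Step 5: size for the comparison.** For 80% power at 0.85 vs 0.75 and r = 0.5, about 63-67 fallers and 212-225 non-fallers would be needed, roughly double the plan.

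**The case against.** The strongest reply has four parts.

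- **No decision rule is stated.** A reader might infer that comparability will be declared because the AUCs look alike or do not differ significantly. The article does not say so. It states an expected result, and the 5% paired test used above is a yardstick that the article does not name. This stands.
- **Detail may sit elsewhere.** The article commits to comparing the tests in the same population, and the choice between DeLong and bootstrap may belong to an analysis plan not shown here. This stands for the choice of method. It does not cover what the article itself fixes: a similarity hypothesis without a margin and a sample size argued from one AUC. A difference test added later would not by itself support a similarity claim.
- **The miss rate depends on correlation.** A reader might take it that a 0.10 gap goes unnoticed about half the time whatever the comparator. That holds only towards the lower correlations. For SPPB, and nearly so for TUG, the protocol's own expectation gives about one third. This stands.
- **The scenario is assumed.** With HAS at 0.85 and the comparator at 0.75, a missed gap understates HAS. If HAS were 0.85 and a comparator 0.95, the miss rate would be only 14-33%. This stands as a limit on the figure. HAS at 0.75 against a comparator at 0.85 would give the same rates as the main scenario, so the less favourable direction is not excluded.

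**Conclusion.** The concern holds in a limited form. Followed as written, the plan gives no basis for concluding that HAS is comparable with TUG, SPPB and GS. It presents values test by test, does not say how close is close enough, and justifies its size only for the HAS AUC against 0.70, for which it is adequate. Under assumed AUCs of 0.85 and 0.75, a paired 5% test would miss the gap in roughly 25-55% of studies for within-group correlations of 0.7 down to 0.3. The paired difference would be known to within about ±0.06 to ±0.12. These figures rest on the assumed comparator AUC, on binormal scores and on reaching 31 fallers and 104 non-fallers.

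A reader might go further and say that the study cannot address comparability at all. The documents do not support that: the paired data will be collected and the difference can be estimated. What is missing is the step from that estimate to the word comparable. The main HAS accuracy question is unaffected.

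**What to change.** In the Part II data analysis section, add the paired AUC difference, HAS minus each of TUG, SPPB and GS, with a 95% confidence interval by DeLong or bootstrap. State there, or in the sample size section, that the planned size resolves AUC differences of only about 0.1. Then choose one of two routes:

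1. State a margin before the data are analysed, and use the word comparable only where the whole interval lies within it; otherwise report the interval without that word.
2. Reword the hypothesis as descriptive, so that the differences are estimated and no similarity claim is made.

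The cost is a few lines of text and analysis on data already planned; no extra participants or visits are needed. The downside is that comparability may not be reachable for every comparator. As an illustration only, with a margin of ±0.10 and both true AUCs equal to 0.85, the whole interval would fall inside the margin in about 19-70% of studies for correlations of 0.3-0.7.

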#### Study design

Part II is a validity study with prospective data collection regarding the external criterion (fall history) and a cross-sectional design for the evaluation of the construct validity.

#### Participants in and exclusion criteria

 People already participating in the AFFIRM-CT study, and having signed informed consent for this part will be included. For part II, community-dwelling and hospitalized participants will be included according to the same inclusion and exclusion criteria as the participants of part I of this study.

#### Procedure

From January 2021 on, participant recruitment is following the same procedure as described in part I until the scheduling of the first appointment after participants signed the informed consent.

During the first appointment, the study nurse will assess the following fall risk related variables: fall history of the last 6 months [6], poly-medication, and participants’ physical activity level assessed with a physical activity tracker worn on the wrist over 7 days. Then a health care professional blinded for participants’ fall history will assess the following functional fall risk assessments: SPPB [24], TUG [38], usual GS [25], and HGS [40]. Afterward, the second assessor blinded to the test results of the functional fall risk assessments and the fall history of the participants will measure participants’ HAS according to the given description of the index test. This assessor will receive prior to the measurements, a short 10min instruction of the use of the dynamometer, similar, to what would be done in a clinical situation. The HAS of the left and right side will be evaluated either by starting with the randomly chosen right or left side. As described in part I, the MVIS will be measured by asking the participants to push as hard as possible with the dynamometer against the wall (3 times per leg with a break of 30 seconds between each trial). Then the measurements are repeated, this time by pushing the dynamometer as fast as possible against the wall (assessment of the RFG).

Once the hip abductors strength (index test) is evaluated, participants will be followed up for a 12 months period to assess their number of falls (reference test). Participants will be provided with fall diaries in which they are asked to write down their falls and the circumstances/reasons of the falls (intrinsic or extrinsic) and occurring injuries (e.g. fractures) every time such an event will happen. Participants’ will thoroughly be explained what the definition of a fall is and how to fill out the fall diary. A fall is defined as an event resulting in a person inadvertently coming to rest on the ground, floor, or other lower level [2]. Every 6 months, the study nurse will call participants to collect the fall information and provide coaching for the fall diaries if needed.

#### Data collection

 Data collection will be performed as soon as the participant officially gave their permission and signed the informed consent. Participants’ information and test results will be entered into the electronic case report form (e-CRF).

##### Socio-demographic data and fall risk assessment

As for part I, the reliability part, the socio-demographic data (age, sex, height, and weight) will be obtained by a phone call or from the electronic participant record of the AFFIRM-CT study. A variety of non-functional fall risk related variables for the description of our participants will be assessed. The fall history of the last 6 months and the MMSE [28] will be evaluated by the study nurse exactly as described in the data collection section of part I of this protocol. The number and names of the medication the participants take will be written down on the participant’s documents to get an indication of their poly-medication. Further, participants’ physical activity level, assessed with a physical activity tracker worn on the wrist over a time span of 7 days, and the use of walking aids/assistive devices will be registered in the e-CRF.

